### Interventions

#### Recapture Life-AYA intervention

Recapture Life is guided by the *Adolescent Resilience Model* (ARM) 
[56]. Based on extensive research in AYAs with cancer, the ARM conceptualises resilience in young people as a multifaceted process, involving the interaction of individual, family and social-level risk and protective factors to determine AYAs level of resilience, and ultimately their quality of life. Additional file 
1: Table S1 identifies the key components of this model and the way in which these processes are targeted in Recapture Life. Several adaptive processes are implicated by this model including AYAs’ ability to: enact positive coping behaviours, negotiate uncertainty in illness and cancer-related distress, reappraise the experience in order to derive adaptive meaning from it, and seek and maintain support from family and friends. To our knowledge, only one other published intervention has utilised this framework in AYAs 
[57,58], however this music therapy intervention is delivered individually to AYAs receiving stem-cell transplants whilst on treatment. As such, this program may not offer the skill-building and peer support that we hypothesise are crucial to promote adaptation into survivorship. In addressing these component processes of resilience after cancer, our manualised program derives its core mechanisms of change from CBT techniques.

The primary goals of the Recapture Life-AYA intervention are to improve QoL, reduce distress and facilitate healthy coping in young cancer survivors. Participants randomised to Recapture Life-AYA will participate in six, weekly, 90-minute sessions facilitated by a psychologist. Each group will comprise the psychologist plus a minimum of 3 and a maximum of 5 AYAs with mixed diagnoses and genders, separated into two age groups: 15–17 and 18–25 years. Each Recapture Life-AYA module applies CBT techniques to the key domains of concern identified by our team’s previous work 
[59,60] (See Additional file 
2: Table S2).

Sessions will be delivered through video-conferencing software on the Internet (WebEx, by Cisco). WebEx videoconferencing requires a computer with standard browser, a high-speed internet connection, and a webcam. WebEx is a secure, password-protected video-conferencing program that allows ≤6 participants to be seen on the screen simultaneously, much like Skype^TM^. Participants will also receive a reminder SMS on their cellular phone 24 hours before their session, which will also serve as their reminder to complete the emotion thermometers tool and homework compliance scale (see *Assessments* section).

Nominated support-person participants receive a workbook describing the program and one group-based 2-hour online session which includes family communication training. Support persons associated with AYAs randomly allocated to receive the Recapture Life-AYA intervention will additionally receive a weekly psycho-educational email, which includes a general overview of some of the skills learnt by the AYAs. These updates are not specific to the individual participant and include examples of (i) ways the support person can support the AYA, and (ii) suggestions for communicating about the weekly topic.

#### Peer-support group (active control)

The PSG control is delivered in an identical manner to Recapture Life-AYA (via WebEx, 3–5 participants/group, with the same facilitator, divided into 2 age groups), frequency of contact (six weekly 90-minute sessions), and the availability of peer-based group discussion. Like Recapture Life-AYA, it also involves age-appropriate supportive counseling to normalise the range of AYA experiences 
[61] and provides AYAs an opportunity to give and receive emotional/practical support. During each session, AYAs are encouraged to exchange information about a nominated topic (closely match those addressed in Recapture Life-AYA, e.g. ‘relationships’). The key distinction between Recapture Life-AYA and the PSG control is that the PSG does not include directive, structured teaching of specific, CBT-based coping skills. The PSG also does not include the support-person element where they receive psychoeducation and weekly emails alongside the AYA online sessions. The PSG in this trial will adhere to best practice guidelines 
[62] and is manualised to ensure standardization across all sessions.

### Procedures

Following recruitment, participants will complete an intake interview with the study psychologist ([name]) to further screen for participant eligibility, orient participants to the study procedures, and ascertain the suitability of the participant’s internet connection. The intake interview will also serve to build rapport with the psychologist, by providing AYAs the opportunity to discuss their cancer experiences, current needs, and personal goals in participating in the study.

Participants will then be randomly allocated to one of the three study arms. The research assistant will send a hired (insured) laptop to any participants who do not have computer access two weeks before the commencement of each online group. This process will ensure equity (all participants will have access to identical equipment), minimise technical challenges (required software/hardware will be pre-installed) and will maximise security (security settings will be pre-set by the technical support person). All equipment will be returned after study participation. Participants randomised to the Recapture Life-AYA condition will also receive a written manual summarising the weekly home practice activities.

During Weeks 1–6 of each 12 week block, those allocated to Recapture Life-AYA and the PSG will participate in their allocated intervention. In Week 7, all participants will complete their second assessment (T2). For waitlist controls, this assessment will also serve as their T1 (pre-intervention) assessment. In Week 7, waitlist participants will be randomly allocated to either Recapture Life-AYA or PSG (completed during weeks 7–12). Waitlist participants will then complete a second T2 assessment, one week after their intervention.

#### Study integrity

This study is listed on the Australian New Zealand Clinical Trials Registry (ACTRN12610000717055), and has undergone rigorous multidisciplinary peer-review. It is endorsed by both the Clinical Oncology Society of Australasia’s (COSA) AYA Cancer Research Steering Committee, as well as the Scientific Advisory Committee of the Psycho-oncology Co-operative Research Group (PoCoG). In addition to having its own study consumer representatives (one male, two female, mean age: 22 years), the Recapture Life-AYA study has also been reviewed by the PC4 and PoCoG Joint Consumer Advisory Group panel, who endorsed the appropriateness and clinical importance of the research question.

Ethical approval has been obtained from the South Eastern Sydney Local Health District (SESLHD) – Northern Sector, Human Research Ethics Committee (HREC Ref: 12/008) for three sites (Centre for Children’s Cancer and Blood Disorders, Sydney Children’s Hospital; Sydney Youth Cancer Service, Prince of Wales Hospital; and the Victorian Adolescent and Young Adult Cancer Service, Peter MacCallum Cancer Centre). Ethical approval for additional sites around Australia will be submitted in July 2012. This study complies with the CONSORT guidelines 
[63] by using: a) standardised assessment measures; b) blind assessments; c) standardised assessor training and inter-rater reliability checks; d) manualised, replicable procedures for all conditions; e) random allocation, and f) treatment fidelity checks.

#### Treatment fidelity

Both treatment groups will be facilitated by the same person to prevent therapist confounds (e.g. therapist attributes such as age, gender and communication style, each of which could impact group retention/efficacy). Any variation or systematic biases between groups will be detected and corrected by the independent assessors during treatment fidelity checks of a random 15% of all video-recorded sessions (the validated ‘Method of Assessing Treatment Delivery’ advises a minimum of 11%) 
[64] All pre- and post-treatment outcome measures will be administered by the study co-ordinator, who will be blind to group allocation. In compliance with the CONSORT guidelines, the assessor will report on which condition they believe each participant was in at the beginning and end of the study.

In addition, to ascertain why this intervention may not be tolerated by all young people, exit interviews will be collected for all who leave the study prematurely, as well as 15% of completers to collect in-depth data on participants’ likes and dislikes and soliciting ideas for improvement.

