#### Participant recruitment

Potential participants aged ≥16 years will be mailed a personalised invitation letter, consent form and opt-in card by their oncologist. Parental consent to approach participants <16 years will be sought. Nominated support persons given the study information by their AYA child/partner may also choose to opt in by returning the consent form. The research assistant will contact all AYA participants who opt in to the study to request that participants sign and return a written contract agreeing to use the provided equipment solely for study purposes and to address internet access issues.

Recruitment will occur in 3x12 week blocks, such that ~80 patients who have completed treatment in the preceding 1–6 months will be invited 4 weeks prior to Week 1 of each block. This recruitment window was chosen to maximise the benefit to participants, by delivering the coping skills intervention early in survivorship. Given the assumed response and attrition rates (see above), it is envisaged that 3 iterations (i.e. 3x12 week blocks), each attracting ~40 AYA opt-ins, will be required to achieve the target sample. This means that 3 mail outs (approaching ~80 patients at a time) will occur for the study during 2012. This design ensures the standardisation of time since treatment completion across arms. All fully consented participants will be telephoned by the study co-ordinator one week prior to Week 1 to administer the Psychosocial Adjustment to Illness Scale (PAIS; T1 assessment). Participants will also complete the first online questionnaire at this time. (See Figure
1 below, for study flowchart).

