#### Psychosocial functioning

There is little consensus regarding the relative superiority of generic versus disease-specific psychosocial measures in psycho-oncology. Disease-specific measures often appeal to researchers due to the difficulty ascertaining ‘clinical’ change in populations that may only be distressed at sub-clinical levels 
[67,68]. However, generic psychological measures facilitate comparison to healthy norms, which is clinically and empirically advantageous 
[29]. As recent reviews have not shown disease-specific measures to provide a systematic advantage in detecting intervention effects 
[29], the Recapture Life-AYA trial uses both generic and disease-specific indicators of psychosocial functioning.

Quality of life (QoL) was selected to be the primary psychosocial outcome variable, as this enabled the measurement of specific functional issues specific to early cancer survivorship. The Impact of Cancer Scale (IOCS) 
[69,70] was chosen to measure QoL, and measures aspects of cancer survivorship such as: Life Challenges, Body/Health, Talking With Parents, Personal Growth, Thinking/Memory Problems, Health Literacy, Socializing and Financial Problems. Although this measure has been validated in 18–39 year old AYA cancer survivors, its readability and content relevance for the younger AYAs in the Recapture Life-AYA trial was confirmed through assessments pilot testing with consumer representatives aged 15–18 years. The Flesch-Kincaid reading level was also assessed as being at Grade 6.15.

There will be a number of secondary psychosocial functioning measures. The *Psychosocial Adjustment to Illness Scale–Interview Form (PAIS)*[71] will be administered to participants over the telephone at each time point. The PAIS assesses psychosocial adjustment of patients to cancer across seven domains including: Health Care Orientation, Vocational Environment, Domestic Environment, Sexual Relationships, Extended Family Relationships, Social Environment and Psychological Distress.

The *Depression, Anxiety and Stress Scale-Short Form (DASS–21)*[48] is included as a brief, generic measure of other relevant symptoms of psychological distress. This scale shows strong internal consistency and reliability for each subscale 
[48,72,73]. The DASS-21 has been validated in Australian adolescents 
[72], and in cancer patients 
[74].

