### Data management and analysis

All measures (except the telephone interview) will be administered online, through Lime Survey^TM^ at all timepoints. This secure tool enables participants’ data to be downloaded to files amenable to statistical analysis, such as the Statistical Package for the Social Sciences (SPSS, by IBM).

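### The blind-assessment claim is worded to cover all outcome measures, but the primary scale and every other online measure are completed by participants who know at T2 whether they were waitlisted

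*Protocol article*

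**What the plan says.** The protocol article makes the blinding claim in two places. Treatment fidelity says: "All pre- and post-treatment outcome measures will be administered by the study co-ordinator, who will be blind to group allocation". It adds that the assessor will record a guess of each participant's condition at the start and end of the study. Study integrity lists, among the ways the trial meets CONSORT, "b) blind assessments; c) standardised assessor training and inter-rater reliability checks".

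The mode of data collection is described elsewhere. Data management and analysis says: "All measures (except the telephone interview) will be administered online, through Lime Survey". Participant recruitment has the co-ordinator telephone participants for the PAIS and then says: "Participants will also complete the first online questionnaire at this time". Psychosocial functioning fixes the primary endpoint: "Quality of life (QoL) was selected to be the primary psychosocial outcome variable", measured by the IOCS. The same section makes the PAIS a secondary measure that "will be administered to participants over the telephone at each time point".

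**The concern.** On a scale the participant completes, the participant is the assessor. Blinding the person who issues the questionnaire does not blind the person who answers it. If the claim is carried into the report as it stands, readers will take the QoL differences between each active arm and the waitlist as blind-assessed, although expectation in the active arms and disappointment in the waitlist could move the scores.

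This matters because hypothesis 1 compares both active arms with the waitlist on QoL, and the Conclusions link clinical availability to a significant QoL improvement. Readers need to know which QoL contrasts are open to this bias.

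**Working it through.** The protocol gives no figure on this point, so the check is a comparison of sections.

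1. **Which measures can be assessor-blind?** Every measure except the telephone interview is online (Data management and analysis). The PAIS is the only measure described as given by telephone (Psychosocial functioning). The IOCS, DASS-21, KIDCOPE and family measures are therefore online.

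2. **Who answers the online measures?** Participant recruitment has the participant complete the online questionnaire, separately from the telephoned PAIS. Psychosocial functioning reports reading-level and readability checks for the IOCS, which fits a scale that respondents read themselves. The article never calls the IOCS self-report; that is inferred from these places together.

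3. **What do participants know at T2?** Under Procedures, the Recapture Life and peer-support arms attend their sessions in Weeks 1–6, and T2 is in Week 7. Waitlist participants have had no sessions by then and are allocated to an active arm in Week 7. Each participant thus knows at T2 whether he or she was waiting. The point concerns T1 to T2; after Week 7 no untreated waitlist remains.

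4. **What does the blinding check test?** It records the assessor's belief about allocation. That bears on scores the assessor elicits, not on scores entered online by the participant.

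5. **Is the PAIS collected after randomisation?** Psychosocial functioning gives it at each time point. Table 1 marks it at intake only, and under Procedures the intake interview precedes random allocation. If Table 1 is right, no interviewer-administered outcome remains at T2 or T3 for blinding to protect. (Table 1 may have suffered in text extraction, and its IOCS row is not relied on here.)

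**Illustration of scale, under assumed values.** Suppose there is no true effect, 30 participants per arm (90 ÷ 3, equal allocation assumed), a two-sided 0.05 test, and a reporting shift of *b* SD between an active arm and the waitlist. The test statistic is shifted by δ = *b*·√(30/2) = 3.873*b*, and the rejection rate is 1 − Φ(1.96 − δ) + Φ(−1.96 − δ).

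| Assumed *b* | Share of target d = 0.65 | δ | Rejection rate (normal) | Noncentral t |
|---|---|---|---|---|
| 0 | 0% | 0 | 5.0% | 5.0% |
| 0.1 | 15% | 0.387 | 6.7% | 6.7% |
| 0.2 | 31% | 0.775 | 12.1% | 11.9% |
| 0.3 | 46% | 1.162 | 21.3% | 20.8% |

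The values of *b* are assumptions, not estimates. The rates ignore the multiplicity adjustment promised under Statistical analyses. They would apply to any unblinded comparison of this size, and rewording the blinding statement does not change them.

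**The case against.** The strongest reply is that the sections can be read together: one says who administers the measures, the other by what medium. A co-ordinator can issue, prompt and chase an online questionnaire, and keeping that person blind stops follow-up from differing by arm. This stands. The co-ordinator's blinding has some value for the online scales, and it would be wrong to say that it gives no protection at all. It does not make the answers blind-assessed, however, and the unqualified entry under Study integrity invites that reading.

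A second reply is that participants cannot be blinded in a trial of group therapy against a waitlist. That also stands. A reader might infer that the protocol claims blinded participants, or that their lack of blinding is itself a fault. The documents support neither: no section says participants are blind, and their knowledge of being on the waitlist is inherent in the design. The fault is the reach of the blinding statement.

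A third reply is that the Discussion already gives the peer-support arm the job of controlling expectation, and gives the waitlist a different one (natural recovery and changes in services). This is correct and should be credited. It helps Recapture Life versus peer support (hypothesis 2). It does not help either active arm versus waitlist (hypothesis 1).

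The point is not an omission that a fuller document might supply; it concerns a statement made in the text shown.

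**Conclusion.** The point holds in a limited form. The article presents blind assessment as covering all pre- and post-treatment outcomes, while its own account of data collection leaves only the PAIS interview for which an assessor's blinding can have that meaning. The primary IOCS is outside it. This rests on inferring from three sections that the IOCS is completed by the participant; no section points the other way.

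The size of any resulting bias is unknown. A reader might take the rates of about 7%, 12% and 21% as the trial's false-positive risk, but they follow from assumed shifts of 0.1, 0.2 and 0.3 SD and should carry no weight in judging severity. Nor do the documents support a conclusion that the trial is invalid: the comparison with peer support is designed to hold expectation similar, and the waitlist contrasts remain interpretable as open-label. The consequence is a safeguard misdescribed for the primary endpoint, which limits what the T1-to-T2 waitlist contrasts can be said to show.

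**What to change.** 1. Reconcile Psychosocial functioning (PAIS at each time point) with Table 1 (intake only). This comes first, because a blinding claim tied to the PAIS is sound only if the PAIS is collected after randomisation.
2. Under Study integrity and Treatment fidelity, limit the blind-assessment claim and the assessor's guess of allocation to the post-randomisation PAIS interview. If useful, say separately that the blind co-ordinator also handles contact and follow-up for the online questionnaires.
3. State that the IOCS and the other online scales are unblinded participant report.
4. Describe the T1-to-T2 contrasts with the waitlist (hypothesis 1) as open-label. Rest any claim about the specific effect of Recapture Life on its comparison with the peer-support group, as the Discussion already implies.

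Items 2 to 4 change wording in the protocol and the report; sample size and analysis model are unaffected. The price is a less favourable description of the waitlist contrasts. Item 1 may also mean correcting either the table or the text.

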#### Safety monitoring

Although research suggests that teaching AYAs CBT-based coping skills is likely to reduce their post-cancer distress 
[29], it is possible that some participants will experience increased short-term distress. This trial includes safety monitoring and management procedures at multiple stages of the project (See Additional file 
3: Table S3, for details). Firstly, the intake interview involves careful screening for acutely suicidal/severely depressed participants at study intake using validated items sourced from the Adolescent Suicide Assessment Protocol 
[65].

Secondly, participants will be regularly screened for deterioration in mood during the trial when they complete the weekly emotion thermometers tool (see *Assessments,* below). Any serious deterioration in mood reported on any study assessment measures will trigger protocols involving contacting the participant to discuss their emotional state, and a meeting between the study researchers to develop a management plan (which may involve contacting their nominated health professional).

### Assessments

The following measures will be administered at all time-points (see Table
1). The study questionnaire has been reviewed by pilot testing with AYA consumers, who report that it is easy to understand and of a reasonable length (completion time <40 minutes for 135 items). Details relating to each measure are presented in Additional file 
4: Table S4.

**Table 1 T1:** Assessment schedule for the Recapture Life-AYA study

**Measure**	**Intake**	**T1**^**a**^	**During intervention**^**b**^	**T2**^**c**^	**T3**^**d**^
Psychosocial Adjustment to Illness Scale-Interview form (PAIS)	**X**	**-**	**-**	**-**	**-**
Demographic data*	**-**	**X**	**-**	**-**	**-**
Emotion thermometers tool*	**X**	**-**	**X**	**X**	**X**
Homework Compliance Scale			**X**	**-**	**-**
Impact of Cancer Scale (IOCS)			**-**	**-**	**-**
Depression, Anxiety, Stress Scales-short form (DASS-21)	**X**	**X**	**-**	**X**	**X**
Centrality of Event Scale-Short Form	**-**	**X**	**-**	**X**	**X**
Perception as “cancer survivor” item	**X**	**X**	**-**	**X**	**X**
McMaster Family Assessment Device*	**-**	**X**	**-**	**X**	**X**
KIDCOPE-Older Version	**-**	**X**	**-**	**X**	**X**
Youth Satisfaction Questionnaire*	**-**	**X**	**-**	**X**	**X**
Intervention satisfaction items*	**-**	**X**	**-**	**X**	**X**

* Measures with an asterisk also used in support-person participants at these same time-points.

^**a**^ T1 = Baseline; ^**b**^During intervention = weekly prior to intervention sessions 2–6; ^**c**^ T2 = post-intervention; ^**d**^ T3 = 12-month follow-up.

